## Abstract

**Background:**

Intimate partner violence (IPV) affects almost one in three women worldwide. However, disclosing violence or seeking help is difficult for affected women. eHealth may represent an effective alternative to the standard support offers, which often require face-to-face interaction, because of easy accessibility and possibility of anonymous usage. In the Netherlands we are developing SAFE, an eHealth intervention for female victims of IPV, which will be evaluated in a randomized controlled trial and a process evaluation, followed by an open feasibility study to assess real-world user data.

**Methods/design:**

The randomized controlled trial is a two-arm parallel design comparing an intervention arm and a control group. The groups both have access to eHealth but differ in the offer of interactive features compared to static information. Both groups complete questionnaires at three or four time points (baseline, three months, six months, 12 months) with self-efficacy at 6 months as the primary outcome, measured with the General Self-Efficacy (GSE) scale. The process evaluation consists of quantitative data (from the website and from web evaluation questionnaires) and qualitative data (from interviews) on how the website was used and the users’ experiences.

**Discussion:**

eHealth has the potential to reach a large number of women who experience IPV. The internet-based design can lower access barriers and encourage help-seeking behavior ultimately reducing the lag time between subjective awareness and protective action.

**Trial registration:**

Trial registered on 15 August 2017 at the Netherlands Trial Register NL7108 (NTR7313).

## Background

Intimate partner violence (IPV) is any physical, sexual, psychological, or economic violence that occurs between former or current partners [1]. While both men and women can suffer from IPV, the majority of victims are female. Worldwide almost one in three women experience IPV in their lifetime [1–3]. Being a victim of IPV has numerous negative consequences at the physical, social and psychological level. For example, a higher risk of developing depression, anxiety disorders, and post-traumatic stress syndrome (PTSS) [4, 5]. In addition, children exposed to IPV are at increased risk for developing trauma and are three times more likely to become a perpetrator or a victim of violence themselves [6–11].

Women report major obstacles in disclosing IPV and seeking help. Delays in help-seeking are related to fear, shame, guilt, loyalty, children, financial dependency, not knowing where to go for help, and not subjectively identifying IPV as such. Attempts to overcome these barriers have had limited effects [12–19]. Even though the governmental and political efforts to decrease IPV and its detrimental effects have substantially increased over the last decades, there is still a need for effective interventions that can reduce the lag time between exposure and active help-seeking.

eHealth is becoming more popular in healthcare [20–22]. For potentially stigmatizing and traumatizing experiences, such as IPV, eHealth represents an ideal option because it is easily accessible, allows anonymity and thereby safety and does not require face-to-face contact [23]. It has the potential of reaching large numbers of women exposed to IPV. Some eHealth offers for women exposed to IPV have already been reported outside of Europe: I-DECIDE in Australia [24], *isafe* in New-Zealand [25], IRIS in the United States [26], and iCAN in Canada [27]. These interventions are completely online based, and all provide a (personalized) safety plan for participants and information on help for IPV. To our knowledge, no such intervention has been developed in Europe to date, although the prevalence rates do not differ from the rest of the world [3]. To fill this gap, we developed an eHealth intervention in the Netherlands, SAFE, to be found at www.safewomen.nl. SAFE was inspired by I-DECIDE [24] and Feel the ViBe, a Dutch internet intervention for youth exposed to family violence [23]. Furthermore, SAFE is based on available scientific knowledge and a national qualitative study on experiences from female survivors and IPV experts ([name] et al., forthcoming). SAFE will be evaluated through a randomized controlled trial, a process evaluation, and an open feasibility study.

### Aims of SAFE: effectiveness, process evaluation and feasibility

The SAFE randomized controlled trial (RCT) is designed to evaluate the effectiveness of an interactive intervention in increasing self-efficacy at six months in women exposed to IPV, compared to a minimal intervention. The secondary outcomes assessed are self-awareness, (mental) health symptoms and perceived support in women exposed to IPV.

The primary aim of the process evaluation is to evaluate the feasibility of SAFE with the following research question:

Is SAFE a suitable tool to provide information and support to women exposed to IPV?

Firstly, we will discuss the study procedure of the RCT. Subsequently the process evaluation and the open feasibility study are described, followed by the discussion.

## RCT methods and design

The RCT investigates two groups: the SAFE group, which receives the complete intervention, and the control group, receiving a minimal intervention as described below. The RCT has a parallel design with randomization balanced on age (18–30 years old and 31–50 years old). The study is conducted in the Netherlands and the intervention is only available in Dutch. The trial is registered at the Netherlands Trial Register (NTR) with trial ID NTR7313. The protocol is described conforming to the CONSORT EHEALTH guidelines [28].

### Sample size calculation

The sample size was calculated based on the primary outcome measure, the General Self-Efficacy Scale (GSE). In the general population, a mean score of 29.3 (SD 4.6) was described [29, 30]. We measure GSE scores at T0 (baseline), T1 (three months), T2 (six months), and T3 (12 months). We consider a difference of at least two points relevant and to detect this difference, 85 participants will be needed (power = 80%, alpha = 5% two-sided testing) in each group at T2 (six months). If we apply an ANCOVA analysis with the T2 measurement as a dependent variable and correct for the T0 measurement, the sample size has to be adjusted with the factor (1 - r^2^) (89). With r as the correlation between T0 and T2. We use *r* = 0.5 which translates into 64 participants in each group. We assume a relatively high attrition rate (35%) at T3. Such an attrition rate is common in eHealth research and similar designs [23, 26, 27, 31–33]. Therefore, we plan to include 99 participants in each group (198 participants in total) at baseline, with an observation period of six till 12 months. Participants included during the period April 2019 – March 2020 will be followed for 12 months, completing surveys at four time points (T0 – T3). Participants included in the extended inclusion period, due to high attrition and low response rates, April 2020 – October 2020, will be followed for six months and completing surveys at three time points (T0 – T2) in order to not interfere with the planned open feasibility study.

### Inclusion and exclusion criteria

Inclusion criteria:
identifying as woman;18–50 years old;self-identifying as a victim of IPV;having access to a computer and internet connection.

Exclusion criteria:
reporting no unhealthy or abusive relationship or experienced fear of partner in the past 12 months at T0;inability to read and understand the Dutch language (all outcome measures are in Dutch);

However, women who are over 50 or who experienced IPV or fear of partner longer than 12 months ago are given access to the control group version of the website. No data will be collected from the excluded participants.

### Recruitment, inclusion and randomization

Participants are mostly recruited online, through social media, Facebook Ads and Google Ads. Several (mental) health organizations (e.g. general practitioners’ offices, emergency rooms, physiotherapists, social workers) are contacted with information about SAFE and provided with a (digital) poster that can be shown in the waiting room.

Women interested in using SAFE must register online and give consent to participate in the study. Women read the patient information letter and check a box to give consent. This is followed by a mandatory 24-h waiting period to ensure participants had sufficient time to contemplate participating in the study. After 24 h they are asked to give consent for a second time and fill out the T0 questionnaires. Subsequently, after checking inclusion criteria, they are randomized automatically. A stratified (block size of four) randomization balancing for age will be performed (Fig. 1). This random allocation sequence with age blocks is generated by the eHealth developer and a statistician. Randomization is single-blind to the participants but not to the researchers. Participants have immediate access to the website after completing the T0 questionnaires.

**Fig. 1 Fig1:**
[figure not shown]
Online inclusion procedure

### Intervention

#### Development

In the development phase we interviewed 16 women to explore wishes and needs as key elements for SAFE. The women were survivors of and/or experts on domestic violence (DV) and IPV. We also assessed women’s needs concerning their safety when using SAFE ([name] et al. forthcoming). With this input, together with other (scientific) sources such as the I-DECIDE study [24], we developed a prototype, which was tested in a focus group of previously interviewed women. The prototype was improved based on the feedback and tested again in a focus group, resulting in a definitive version of the intervention used in this RCT.

#### Structure of the intervention

The SAFE intervention contains various modules and means of contact. The full intervention consists of four modules (Table 1). The modules provide information, tips, and exercises. Information that SAFE provides is based on scientific research and on information provided by IPV and DV help or research organizations.

**Table 1 Tab1:** SAFE modules and functionalities

***My situation (module)***	***Help (module)***
*Intimate partner violence (IPV)*	*Help options*
*Relationships (healthy and unhealthy)*	*Help database*
*Impact on children*	*Safety*
**My health (module)**	**My environment (module)**
Physical health	Social support
Mental health	Contact
Symptoms and tips	Disclosing IPV
***Contact***	***About SAFE***
*Contact options with fellow survivors and victims*	*Patient information letter*
*Contact with community managers*	*Safety measures*
Chat, forum and diary	*Organizations involved*
	*Community managers*
***Additional functionalities (throughout the intervention when applicable)***	
Short videos (‘vlogs’) with survivors and professionals	
Quotes and stories from survivors	
Exercises	
*Tips for books, films, activities etc.*	

Note: The Minimal Intervention consists solely of the cursive components; the SAFE intervention consists of all mentioned components (cursive and non-cursive)

Community managers (CMs) manage the website and the registrations. Participants can use the website anonymously, for free, and as much as they want, without following a specific order as we take into account the differences in the individuals’ situations and needs. We do advise to start at the ‘Start here’ page where participants can find an explanation on how the website works. Furthermore, with a pop-up we advise on 24/7 help options in case of emergencies and on safely using the internet and SAFE.

CMs are (mental) health professionals or trainees supervised by (mental) health professionals. Participants can reach the CMs through e-mail, contact form, chat or forum. However, SAFE remains a self-support intervention, meaning the CMs do not initiate contact with participants, other than within the themed chats. Participants receive automated e-mails with a neutral name (“update from your menstrual calendar”), guiding them through the informed consent process and the questionnaires.

The website launched on April 1st 2019 and is locked during the RCT. Components that are still dynamic during the RCT are the chat, forum, pages with news and tips for books etc., and the help database. Bug fixes and downtimes will be registered.

### Outcome-measures

Participants are invited to complete surveys at three or four points in time: at registration (T0), at three months (T1), at six months (T2), and at 12 months (T3; only for participants in the first inclusion group). A Web Evaluation Questionnaire is completed after one month and at T2. The primary outcome is self-efficacy at six months, measured with the General Self Efficacy Scale (GSE). This scale assesses perceived self-efficacy in coping ability and adaptation to stressful life events [29, 30, 34]. We hypothesize that the intervention group will score a higher mean self-efficacy score than the comparison group at six months post-baseline.

The secondary outcomes are anxiety and depression, awareness, perceived social support, fear of partner, and perceived support from the website (Table 2).

**Table 2 Tab2:** Secondary outcome measures

Outcome	Measure	Description	Hypothesis
Anxiety and depression	Hospital Anxiety and Depression Scale (HADS)	To determine levels of experienced anxiety and depression symptoms [35–37].	Participants in the intervention group will show a lower mean depression score and a lower mean anxiety score than the comparison group.
Awareness	Contemplation Ladder (modified version; original by Biener & Abrams [38])	To measure awareness of abuse from 0 to 10 based on how ready the woman is to make changes to her situation.	Participants in the intervention group will show a higher mean score on awareness than the comparison group.
Perceived social support	Medical Outcomes Survey – Social Support (MOS-SS5)	The questions concern the access to support of women to persons in their life [39, 40].	Participants in the intervention group will show a higher mean score on perceived social support than the comparison group.
Fear of partner	Visual Analogue Scale (VAS)	To measure the current level of fear of their (ex-) partner from 0 to 10.	Participants in the intervention group will show a lower mean fearfulness score than the comparison group.
Perceived website support	Visual Analogue Scale (VAS)	To measure how supported the participant feels by the website from 0 to 10.	Participants in the intervention group will show a higher mean score on perceived website support than the comparison group.

Other outcomes are general characteristics, measured by the General Characteristics Questionnaire (GCQ) and masculinity-femininity and gender roles, measured with the Bem Sex Role Inventory (BSRI) [41–43]. The impression and use of the intervention are assessed with the Web Evaluation Questionnaire (WEQ), including questions on relevance, language, lay-out, understandability, completeness, structure, findability and ease of use [44].

### Statistical analysis

Characteristics of the intervention and the comparison group will be assessed to study comparability of the groups. Missing data is expected to occur frequently in an internet-based self-support intervention because of loss-to-attrition. Missing data will be examined prior to analysis and the option of multiple imputation will be evaluated.

In the statistical analysis we will use an ANCOVA model and a Generalized Estimation Equation (GEE) model to analyze repeated measures. These models consider that the measures are clustered within a participant. The GEE model can test the difference in effect between the SAFE group and the Minimal Intervention group at different times of measuring.

As a sensitivity analysis, we will also perform complete case analyses. In both cases, we will use an ANCOVA analysis corrected for baseline to assess the intervention effect on short (T1) and long (T2 and T3) term. Following, we will look for the role of gender (derived from BSRI and General Characteristics data) as an outcomes modulator. Gender does not necessarily correlate with biological sex [45] and might be an independent predictor of outcomes [46]. A *p*-value of < 0.05 is considered statistically significant, based on two sided tests. Regardless of these formal significance levels, all results will be reported with corresponding *p* values to allow for situational judgment by the reader. All analysis will be performed is SPSS version 25.

A data management plan has been made which will be monitored independently to ensure safety of data and proper execution of the RCT. Personal information will be coded and the key to the code is only accessible for the project leader, the project coordinator and the research assistant. The quantitative data from questionnaires will be anonymized and other quantitative data as well as qualitative data will be pseudonymized. The data will be kept for 15 years.

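### Randomisation is stratified by age group, but the analysis text names only the T0 score as an adjustment; stating the age stratum as a covariate is a free, modest gain if age is prognostic

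*Protocol article*

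**What the plan says.** The section on RCT methods and design describes "randomization balanced on age (18–30 years old and 31–50 years old". The section on recruitment, inclusion and randomization gives the mechanism: "A stratified (block size of four) randomization balancing for age will be performed". Age group is therefore a design factor.

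The Statistical analysis section names two models: "we will use an ANCOVA model and a Generalized Estimation Equation (GEE) model to analyze repeated measures". For the treatment effect at the short and long term it says "In both cases, we will use an ANCOVA analysis corrected for baseline to assess the intervention effect". The meaning of baseline is clear from the sample size section: "If we apply an ANCOVA analysis with the T2 measurement as a dependent variable and correct for the T0 measurement". The variance reduction taken there, the factor 1 − r², is for that one covariate.

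None of these places names the age stratum as a model term. Nor does the sentence on possible multiple imputation. Gender is mentioned, as a possible modulator of outcome, but the stratification factor is not. The text also does not exclude age: it nowhere says that the T0 score is the sole covariate.

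**The concern.** Stratified blocks force the two arms to have nearly the same age mix. If age group is related to the outcome, this removes the between-stratum part of the variation from the treatment contrast. A model without age leaves that part in the residual, so the reported standard error is larger than the true one. The error is on the conservative side: intervals are wider than they need be, and the test rejects less often than 5% under the null.

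Attrition adds a second reason. Blocks balance age among the women randomised, not among those who return T2 data. The T0 score corrects an age imbalance among responders only as far as age acts through that score.

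At stake is a little precision, in a trial sized at about 80% power that expects to lose 35% of its participants. Type I error control is not at stake.

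**Working it through.** **Inputs from the protocol article (Sample size calculation).** "a mean score of 29.3 (SD 4.6) was described"; relevant difference 2 points; two-sided alpha 5%; power 80%; r = 0.5 between T0 and T2; 64 per group analysed; 35% attrition; 99 per group randomised.

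**Input not in the document.** The share R² of the T2 residual variance (given T0) that age group explains. This is an assumption, shown over a range.

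**1. The plan's own figures**
- Unadjusted: n = 2 × [4.6 × (1.960 + 0.842) / 2]² = 83.04, so 84 per group by the normal approximation. The plan states 85, which is within tolerance.
- ANCOVA factor: 85 × (1 − 0.5²) = 63.75, rounded up to 64.
- Attrition: 64 / 0.65 = 98.5, rounded up to 99.

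The figures reproduce, and none of them uses age.

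**2. Standard error without the age term, balanced strata**
- Residual SD = 4.6 × √0.75 = 3.98.
- Reported SE = 3.98 × √(2/64) = 0.704.
- True SE = 0.704 × √(1 − R²).
- Excess of reported over true SE = 1/√(1 − R²) − 1.
- True type I error = 2 × [1 − Φ(1.96 / √(1 − R²))].
- Power without age = Φ[(2 − 1.96 × 0.704) / true SE].
- Power with age = Φ[2 / true SE − 1.96].

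| Assumed R² | True SE | Reported SE too wide by | Type I error without age | Power without age | Power with age | Points forgone |
|---|---|---|---|---|---|---|
| 0% | 0.704 | 0% | 0.050 | 81.1% | 81.1% | 0 |
| 2% | 0.697 | 1.0% | 0.048 | 81.3% | 81.8% | 0.5 |
| 5% | 0.686 | 2.6% | 0.044 | 81.7% | 83.0% | 1.3 |
| 10% | 0.668 | 5.4% | 0.039 | 82.3% | 84.9% | 2.6 |

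With the t distribution instead of the normal, power is about half a point lower throughout (80.5% at R² = 0) and the differences are essentially the same. Power without age also rises down the table, because balance makes the estimate itself more precise. The fair comparison is therefore along each row, not against a fixed value of about 81%.

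**3. After dropout.** Simulation: 198 women, strata assumed 50/50, blocks of four, 35% random dropout, 6,000 runs per setting, each setting run with a true difference of 0 and of 2.
- Partial correlation 0.2 (R² = 4%): average reported SE without age 0.705, against an actual spread of 0.694 to 0.696, an excess of about 1.5%. Type I error was 0.048 without age and 0.049 with it.
- Partial correlation 0.3 (R² = 9%): 0.706 to 0.707 against 0.691 to 0.695, an excess of about 2%. Type I error was 0.044 without age and 0.051 with it.

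The balanced formula gives excesses of 2.1% and 4.8% for the same two cases, so dropout shrinks the overstatement. Power does not follow: it was 80.5% without age against 81.8% with it at 0.2, and 79.8% against 82.6% at 0.3. Once dropout loosens the balance, part of the age variation really enters the treatment contrast, and only a model with age removes it.

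These calculations are for the ANCOVA. The GEE was not computed separately.

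**The case against.** The strongest objection is that this is a condensed article. A full covariate list is the sort of detail left to a full protocol or analysis plan, neither of which is shown, and the T0 correction in the sample size section is there to justify the factor 1 − r², not to list every term. That stands in part. A reader might infer that the plan adjusts for the T0 score alone, but the text does not say so and age may be listed elsewhere. What remains is that the article does describe the model, names its adjustment variable in two places and leaves out the factor it stratifies on.

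Second, a reader might infer that the standard errors are certainly too wide. They are so only if age group predicts T2 self-efficacy beyond T0, and nothing in the document shows that. At no association the excess is zero.

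Third, a reader might infer that the benefit of stratifying is wholly lost. It is not: the model without age keeps part of the gain, as the power column shows. The planned size never counted on age, so planned power is not reduced.

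Fourth, age imbalance that arises from random dropout is ordinary chance imbalance and is covered by the standard error. That is right. An age term then improves precision; no bias has been shown.

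**Conclusion.** The point holds in a small, conditional form. The design stratifies on age, and the analysis as described does not name age. If age group explains 2% to 10% of the residual variance, leaving it out makes intervals about 1% to 5% too wide with balanced strata, puts true type I error at about 4% to 5%, and forgoes about 0.5 to 2.6 points of power. With 35% random dropout the excess width falls to about 1.5% to 2% at 4% to 9% of variance, while the power forgone stays of the same order. If age is not prognostic given T0, nothing is lost.

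The results rest on the assumed share of variance, 64 analysed per arm, the plan's SD and correlation and, in the simulation, equal strata and dropout unrelated to arm, age or outcome.

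It would be tempting to call the primary test invalid or the trial underpowered. The document supports neither: type I error does not exceed the nominal 5%, the direction is conservative, and 85, 64 and 99 per group stand. This is a free improvement, not a correction of an error.

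**What to change.** State in the analysis text that the randomisation stratum (18–30 or 31–50 years) enters the ANCOVA and the GEE as a fixed covariate, beside the T0 value of the outcome. Include the same term in any multiple imputation model, and in the complete-case analyses. If an unpublished analysis plan already does this, a confirming sentence is enough.

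The cost is one line of text and one degree of freedom. No extra data are needed, since the stratum is known for every randomised woman, and the sample size need not change. Fixing the term before the outcome data are analysed also removes a later choice between results with and without age.
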